#### The intervention group

The eHealth application, which replaces part of the face-to-face contacts, will only be used by the intervention group. In-person contact will be limited to one individual intake meeting and three group meetings. The eHealth application is a mobile diet app, which was developed earlier and has already been pilot tested. In this app, the steps of the diet-intervention will be explained via text and infographics. Participants will receive recipes and tips useful for the different stages of the diet. Exercise is encouraged with personal goal setting, using the national guidelines for exercise [18], and challenges. Personal goal setting with respect to diet, exercise, weight, body composition, glucose levels, medication use, physical complaints, and quality of life will be used and monitored within the app. Moreover, participants will receive daily motivational messages to keep them on-track. To make the app more interactive, the participants can use a chat-function with the dietician, once a week for the first 10 weeks; thereafter, the dietitian will be available every other week for the chat feature in the app. The app is end-to-end encrypted, according to the national privacy guidelines.

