### Data collection and management

#### Plans for assessment and collection of outcomes {18a}

Outcome data will be collected in a case report form designed in a data management system (Castor EDC®). Questionnaires will be sent digitally to participants using Castor EDC®. To promote data quality of the measurements, all researchers will be trained to perform the measurements. To ensure the data quality of the questionnaires, these will be checked by the researcher to see if there are any irregularities.

Study instruments used:Weight will be measured using a Seca 888 compact digital flat scaleCosts will be measured by the Trimbos/iMTA Questionnaire for Costs (TiC-P)Quality of life will be measured with the EuroQol questionnaire EQ-5D-5LBlood pressure will be measured using the Omron, M4-IFood intake will be measured using dietary history [27]Physical activity will be measured by wearing an Activ8 sensor (BV, Valkenswaard, The Netherlands) for 1 week. The sensor will measure non-wear, sitting, standing, walking, cycling, or running in counts per 20 sWaist circumference will be measured with a centimetreBody composition will be measured with the Bodystat Quadscan 4000, Euromedix, Leuven, BelgiumResting energy expenditure will be measured using the Q-NRG, Cosmed Benelux B.V., Nieuwegein, The Netherlands. Patient satisfaction will be measured via the Diabetes Treatment Satisfaction Questionnaire (DTSQ) [28, 29]Attitudes towards using eHealth (general and specific for this diet app) to access health information, measured via the eHealth Impact Questionnaire (EHIQ) [30]Depression and anxiety via the Hospital Anxiety and Depression Scale (HADS) [31]Adherence will be measured with log-on information of the appCompliance with the diet will be measured by analysing dietary history (energy intake compared to advised energy intake in %)Attrition will be measured by the number of participants that drop-out (categorised by reason for drop-out). Practical use of the intervention diet-app, via self-developed questionnaire, focus groups, and the System Usability Scale (SUS) [32]Demographic variables, drug use, smoking and drinking habits, exercise, and medication use will be measured using a self-developed questionnaire.

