### Statistical methods

#### Statistical methods for primary and secondary outcomes {20a}

All analyses will be conducted according to the intention-to-treat principle. Normality of the data and homogeneity of variances will be tested using Shapiro–Wilk test and Levene’s test. As measures of central tendency for numerical data, we will use the mean (in case of normal distribution) and median values (in case of non-normal distribution), with respectively the standard deviation and interquartile range as measures of dispersion.

The primary endpoint will be defined as the between group difference in relative weight change during 12 months. The relative weight change will be analysed with a general linear model for repeated measurements, with independent variables treatment arm, time point (T1, T2, or T3), hospital, and the interaction between treatment arm and time point. The within patient correlations will be modelled using an unstructured covariance matrix. The estimated difference between treatment arms (intervention minus control) in the relative weight change at T3 (12 months) will be calculated using the estimated marginal means. Non-inferiority will be concluded if the upper limit of the 95% confidence interval of this estimated difference remains below the stated non-inferiority margin of 3.0%. When non-inferiority has been demonstrated, the costs and effects will be expressed in the savings per percent weight reduction/patients who successfully lost weight, by means of a probabilistic model, so that the likely skewed data on costs can be considered.

For the secondary analyses of the efficacy outcomes cardiovascular risk factors (lipids), quality of life (EQ-5L), patient satisfaction (DTSQ), attrition (drop-out), and compliance (log-on information and kcal intake vs advised), we will use analysis of covariance (ANCOVA) models. The dependent variable in these models will be the outcome at T1, T2, or T3, and the independent variables will be treatment arm, the outcome at baseline (T0), and hospital. The secondary analyses are exploratory in nature as the power calculation is based on the primary outcome.

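### The baseline-adjusted two-arm ANCOVA named for drop-out and app log-on suits neither: log-on exists in one arm only, and drop-out is binary with a constant baseline value

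*Protocol article*

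**What the plan says.** All references are to the protocol article.

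- **Model.** Statistical methods {20a} lists lipids, quality of life and satisfaction, then adds: "attrition (drop-out), and compliance (log-on information and kcal intake vs advised), we will use analysis of covariance (ANCOVA) models". The dependent variable is the outcome at a follow-up visit, and "the independent variables will be treatment arm, the outcome at baseline (T0), and hospital".
- **Log-on.** The description of the intervention group says: "The eHealth application, which replaces part of the face-to-face contacts, will only be used by the intervention group". Section {18a} calls log-on a measure of adherence; {20a} files it under compliance.
- **Drop-out.** Section {18a} says: "Attrition will be measured by the number of participants that drop-out", with reasons categorised.
- **Objective.** Objectives {7} includes, as a secondary aim, a comparison with VLED on satisfaction and on attrition/compliance.
- **Other measures under that aim.** "Patient satisfaction will be measured via the Diabetes Treatment Satisfaction Questionnaire (DTSQ"), and diet compliance is energy intake from the dietary history as a percentage of what was advised. Table 1 schedules the DTSQ at the start and at weeks 10, 20 and 52, and dietary history at the start and at weeks 10 and 52.
- **Status.** "The secondary analyses are exploratory in nature as the power calculation is based on the primary outcome".

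Visits are given here in weeks because {20a} uses T3 for 12 months, whereas Table 1 uses T3 for week 30 and T4 for week 52.

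**The concern.** One model is prescribed for outcomes of different kinds. An ANCOVA of this form needs a roughly continuous outcome, observed in both arms, with a baseline value that varies between patients. Log-on fails the second condition. Drop-out fails the first and the third.

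This is a stated analysis that does not work, so it cannot be excused as detail that a condensed article leaves to the full plan. No other model is given for either outcome. If the text stands, the analyst must improvise on both after seeing the data. The trial replaces part of the face-to-face contact with an app, so whether patients stay in the programme equally well is one of its natural questions and deserves a method fixed in advance.

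**Working it through.** **The plan's own figures.** No sample size is given for attrition or compliance. The stated 33 per arm for the primary comparison reproduces: 2 × (1.96 + 0.84)² × 7.2² / (3 + 2)² ≈ 32.5, rounded up to 33. The present point does not depend on it. The inputs used below are 80 patients, 40 per arm, three centres, eight groups of ten, and 20% anticipated drop-out (Sample size {14}, Sequence generation {16a}).

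**Layout for the check.** Sequence generation {16a} implies two centres with three groups and one with two, that is 30, 30 and 20 patients. An illustrative allocation with 40 per arm was used, with intervention patients in every centre. The model has five columns: intercept, arm, T0 outcome and two hospital indicators.

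**Drop-out.**
1. Every patient has the T0 value 0, so that column is all zeros.
2. The matrix has 5 columns and rank 4. The baseline coefficient cannot be estimated.
3. Without that term, arm and hospital can be estimated. The arm coefficient is a difference in drop-out proportions, but it comes from a model assuming normal errors of equal variance. A yes/no outcome has variance p(1 − p), which changes with the risk.

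**Log-on.**
1. Only the 40 E-VLED patients have data, so the arm column equals the intercept.
2. There is no use of the trial app before the start, so the T0 column is again constant at zero.
3. The matrix has 5 columns and rank 3. Without the baseline term it has 4 columns and still rank 3. Arm cannot be separated from the intercept, and no recoding changes this.

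**Other outcomes under the same objective.** The DTSQ is numerical, planned in both arms and scheduled at the start and at each follow-up, so the model can be fitted. Calorie intake against advised intake is numerical, planned in both arms and has a dietary history at the start, so it can be fitted at weeks 10 and 52. It cannot be fitted at week 20, when no dietary history is scheduled.

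**Precision of an attrition comparison.** With 40 per arm, equal risk p in both arms and no allowance for clustering, the 95% half-width is 1.96 × √(2p(1 − p)/40):

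| Assumed drop-out in both arms | Half-width |
|---|---|
| 10% | 13 points |
| 20% | 18 points |
| 30% | 20 points |

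Positive correlation within the groups of ten would widen these intervals.

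**Patients absent from a 12-month ANCOVA.** 0.20 × 80 = 16 at most, if all anticipated drop-outs lack a week-52 value. The timing of drop-out is not given, so the number with an earlier follow-up value is unknown.

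**The case against.** The strongest reply is that little is lost. Software would discard the constant baseline term for drop-out, and what remains is a linear model whose arm coefficient is a risk difference. Drop-outs are counted by reason whatever model is used. The secondary analyses are exploratory, and the primary outcome has its own repeated-measures model. Visit-by-visit ANCOVA is also a standard choice for the continuous outcomes. All of this stands, and it limits the weight of the point. It does not rescue the log-on comparison, and the model that would actually be run for drop-out is not the one written.

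A reader might infer more than the document supports:

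- **That the whole secondary objective cannot be answered.** It can in part: satisfaction and calorie compliance fit the stated model.
- **That calorie compliance has no T0 value.** Dietary history is scheduled at the start and the advised intake is set out in the protocol, so a T0 value can be computed. Whether it means compliance before the diet begins is a matter of interpretation, but it can serve as a covariate.
- **That attrition is the main threat to the non-inferiority claim.** Nothing in the document establishes this, and changing the model for attrition as a secondary outcome leaves the primary result as it is.
- **That all 16 expected drop-outs would have earlier measurements to recover.** Some may leave before week 10.
- **That session attendance could stand in as a compliance measure.** It is not a listed measure, and the arms have different schedules (three group meetings against five).

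**Conclusion.** The point holds for two components of one secondary objective. For log-on, the between-arm comparison is impossible, with 0 of 40 control patients able to contribute. For drop-out, the baseline term cannot be estimated and the error model is mis-specified, although a between-arm difference is obtainable once that term is removed. The rest of the objective and the primary non-inferiority conclusion are unaffected.

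The conclusion rests on two readings of the text: that only E-VLED patients use the app, as stated, and that drop-out is recorded per patient as yes or no, which follows from its definition as a count of participants. The exact ranks assume intervention patients in every centre; the failure to identify an arm effect on log-on does not depend on this. The point is worth correcting before analysis because the correction is cheap, but its weight is modest given the exploratory status.

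**What to change.** Amend the secondary-analysis paragraph of {20a}:

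1. **Attrition.** Report the between-arm risk difference with a 95% confidence interval, adjusted for centre, with no baseline term. Allow for the randomised groups of ten where feasible. With eight groups and about 16 expected drop-outs such a model may be unstable, so state in advance what will be reported if it cannot be fitted.
2. **Log-on.** Describe it within the E-VLED arm only, and use one term for it (adherence or compliance) throughout.
3. **Between-arm compliance.** Use calorie intake against advised intake at weeks 10 and 52, the follow-up visits with dietary history. T0 intake may be kept as a covariate.
4. **Optional.** Analyse the continuous secondary outcomes with the primary repeated-measures model plus the T0 value, so that patients who leave after an earlier follow-up visit still contribute. The gain cannot be sized from the document: up to 16 of 80 would be missing from a 12-month ANCOVA, and how many of them would have earlier follow-up data is not stated.

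The cost is wording only. No new data, visits or patients are needed.

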### Sample size {14}

In our previous study using the same diet intervention [5], the standard deviation of the difference in weight loss at 12 months was 7.58 kg, and the baseline weight was 105 kg; thus, the standard deviation percentage weight loss was 7.2%. In the field of long-term weight loss, two weight loss percentages are considered clinically relevant, 3% and 5% [22–24]. In order to stay on the safe side, we choose the non-inferiority margin based on the lower of these two percentages, i.e. a non-inferiority margin of 3%. Results of recently published randomised controlled trials on dietary eHealth interventions [25, 26] have yielded estimates for the percentage weight loss due to these interventions. In light of these results, we assumed in the power analysis that the weight loss percentage is 2% greater in the intervention arm than in the control arm. This estimate of 2% was obtained by averaging the results of Katula et al. (− 3.4%) and Baer et al. (1.1%). Based on a one-sided alpha of 0.025, power set at 0.80, we calculated that at least 33 participants in each study group are required for the present study (calculated using R). Anticipating a drop-out of 20%, based on attrition data of the POWER study, we aim for the inclusion of 80 participants (40 participants per group).

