### Methods in analysis to handle protocol non-adherence and any statistical methods to handle missing data {20c}

Data will be analysed based on the intention-to-treat principle. The general linear model takes drop out under the missing at random assumption into account.

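### The 12-month secondary ANCOVAs leave out patients who drop out and ignore their interim values; a repeated-measures model would use them

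*Protocol article*

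**What the plan says.** Section {20a} of the protocol article sets out two kinds of model.

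- **Weight (primary):** "The relative weight change will be analysed with a general linear model for repeated measurements", with arm, time point, hospital and arm-by-time as predictors. "The within patient correlations will be modelled using an unstructured covariance matrix".
- **Secondary efficacy outcomes** (lipids, quality of life, satisfaction, attrition, compliance): "we will use analysis of covariance (ANCOVA) models". Each is fitted to a single visit: "The dependent variable in these models will be the outcome at T1, T2, or T3, and the independent variables will be treatment arm, the outcome" (its baseline value is meant) and hospital. No other post-baseline value enters.

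The same section states: "All analyses will be conducted according to the intention-to-treat principle". It also calls the secondary analyses exploratory. On missing data, section {20c} repeats the intention-to-treat principle and adds only: "The general linear model takes drop out under the missing at random assumption into account".

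On attrition, section {14} says: "Anticipating a drop-out of 20%, based on attrition data of the POWER study, we aim for the inclusion of 80 participants (40 participants per group"). Section {11b} says that withdrawn participants are not replaced.

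Table 1 schedules laboratory tests, EQ-5D-5L and DTSQ at the start and at weeks 10, 20 and 52. Dietary history is taken at the start and at weeks 10 and 52, but not at week 20. Section {20a} labels the 12-month visit T3 and Table 1 labels it T4, so visits are named by week below.

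**The concern.** A repeated-measures likelihood model handles drop-out under missing at random because it models the interim and final values jointly. A patient who leaves after week 20 still contributes to the 12-month estimate through the week-10 and week-20 values. An ANCOVA of the 12-month value on arm, baseline and hospital has no such route: without a 12-month value the patient is not in the model, whatever was recorded earlier. The plan gives the first model to weight and the second to the secondary outcomes, and its one sentence on drop-out fits only the first.

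Two things are at stake for the 12-month secondary comparisons. Precision is lost because observed data are set aside. There may also be bias if leaving depends on how the patient was doing at week 10 or 20 and does so differently in the two arms. The arms differ in the amount of personal contact and the trial is open label, so such a difference is conceivable, but the protocol gives no data on it. In addition, the 12-month weight result and the 12-month secondary results would draw on different sets of patients.

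**Working it through.** **1. The plan's own figure.** Section {14} gives an SD of 7.2%, a margin of 3%, an assumed advantage of 2%, one-sided alpha 0.025 and power 0.80.

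n per arm = 2 × [7.2 × (1.960 + 0.842) / (3 + 2)]² = 32.55, rounded up to 33. This matches the protocol. The present point changes no sample-size figure.

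**2. Patients in a 12-month ANCOVA.** At 20% drop-out, 80 × 0.8 = 64 patients (32 per arm) have a 12-month value, and 80 − 64 = 16 do not.

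**3. Precision against complete data.**
- SE ratio = √(80/64) = 1.118, so about 12% larger.
- Detectable difference (two-sided 0.05, 80% power, no covariate gain) = (1.960 + 0.842) × √(2/n). This is 0.63 SD with n = 40 per arm and 0.70 SD with n = 32.

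A repeated-measures model cannot recover all of this. Step 4 shows how much it recovers.

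**4. ANCOVA against a likelihood estimate that also uses the week-20 value.** The protocol gives no within-patient correlations, drop-out timing or drop-out mechanism for these outcomes, so all of these are assumptions. Settings: 3,000 simulated trials each, 40 independent patients per arm, true effect 0, outcome SD 1, baseline correlation 0.5, 20% drop-out, all after week 20. Rho is the correlation between week 20 and week 52. The slope is the log-odds of drop-out per SD of the week-20 value.

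| Drop-out mechanism | Rho | ANCOVA bias (SD) | SE, likelihood / ANCOVA |
|---|---|---|---|
| Completely random | 0.7–0.9 | about 0 | 0.92–0.97 |
| Slope 1 in both arms, same rate | 0.7–0.9 | about 0 | 0.95–0.98 |
| Slope 1 in one arm only | 0.7 / 0.8 / 0.9 | −0.082 / −0.094 / −0.111 | 0.94–0.985 (this row and the next) |
| Slope 1.5 in one arm only | 0.7 / 0.8 / 0.9 | −0.100 / −0.124 / −0.152 | as above |

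The ANCOVA SE is 0.21–0.22 SD, so the one-arm biases are about 0.4–0.7 of a standard error (0.082/0.216 = 0.38; 0.152/0.215 = 0.71). The likelihood estimate has bias of at most 0.006 SD.

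**5. Milder settings.**
- Rho 0.7, slope 1 in one arm, all drop-out after week 20 (a separate run of 2,500 trials): bias −0.074 SD, SE ratio 0.97.
- The same, with half of the drop-outs leaving at random before any post-baseline value: −0.047 SD, SE ratio 0.99.
- The same, with three quarters leaving early: −0.026 SD, SE ratio 0.99.
- Slopes of 0.5 and 1 in the two arms, all late: −0.033 SD.
- Large-sample check with equal correlation of 0.5 or 0.7 between all visits: 0.03–0.09 SD when the mechanism or the rate (10% against 30%) differs by arm; about 0 when both are the same. An analysis that also uses the week-10 and week-20 values has bias of about 0 throughout.

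**6. Summary.** Where mechanism and rate are alike in both arms, the cost is precision only. Across all settings the likelihood SE is about 1–8% smaller. Where they differ by arm, bias is about 0.03–0.15 SD.

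**The case against.** The other side has a good case on several counts.

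- **No contradiction in the text.** A reader might infer that the protocol says the secondary models handle drop-out, or that these ANCOVAs break the intention-to-treat rule. Neither follows. Section {20c} speaks of the general linear model, a term that section {20a} uses only for weight, and the sentence is true of that model. Intention-to-treat in the sense of analysis by allocated arm is compatible with ANCOVA. This stands.
- **Deletion is not stated.** The protocol does not say that patients are dropped, and ANCOVA after multiple imputation would fit the same sentence. Such detail is often left to an analysis plan. This stands in part: the lack of an imputation method is not the point. The point is that model, dependent variable and covariates are fixed, and as written they make no use of interim values that are collected.
- **Validity is not all or nothing.** It is tempting to say that the ANCOVA is valid only if drop-out is unrelated to the interim response. That is too strong. With the same dependence and rate in both arms, the simulated contrast has no bias.
- **The larger biases need favourable assumptions:** dependence in one arm only, high correlation and late drop-out. Patients who leave before week 10 add no post-baseline value to either model.
- **Clustering.** Section {16a} allocates whole groups of ten. With an assumed intraclass correlation of 0.05, the SE rises to about 0.27 SD, and a bias of 0.08 SD is then about 0.3 of a standard error.
- **Stakes.** The outcomes are declared exploratory.

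These objections limit the size and severity. They do not remove the case for using the interim data.

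**Conclusion.** The point holds as a modest improvement, not as an error that endangers the trial. The certain part is textual: the secondary models use one post-baseline time point each, and the protocol's drop-out statement does not reach them. Under the planned 20% drop-out, about 16 of 80 patients are absent from a 12-month ANCOVA. That 20% is a planning figure from an earlier study, not a measured rate of missing values for these outcomes.

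Bias is conditional: it needs drop-out that depends on the interim response differently by arm, or at different rates. The documents neither show nor exclude this, and the 0.03–0.15 SD range rests entirely on assumed settings. The non-inferiority conclusion on weight and the sample size are untouched.

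**What to change.** For the continuous secondary outcomes measured at weeks 10, 20 and 52 (lipids, EQ-5D-5L, DTSQ), replace the separate ANCOVAs by one repeated-measures model per outcome. Include arm, time, arm-by-time, hospital, the baseline value and baseline-by-time, with unstructured covariance, and read the arm contrast at each visit from that model. It is the same class of model as for weight, but not identical: the weight model has no baseline covariate. The drop-out statement in section {20c} would then apply to these outcomes too.

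Attrition and app log-ons are outside this change. Compliance by energy intake needs its own wording, because dietary history is not taken at week 20.

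The cost is a change of wording and a little more analysis work. No extra data, visits or patients are needed.
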